## Recruitment {15}

As we have completed several clinical trials in secondary schools previously, the number of schools for achieving the target sample size will be secured from previous collaborators. Considering the refusal rate was around 20% in our previous studies, one class (class size is around 30 to 40 students) in each Form II, III, and IV will be purposely selected and invited to join the study via school. The sample size of 900 is assumed to achieve by contacting a total of 12 (school)× 3 (grade)× 30~40 (student) = 1080~1440 students initially.

## Assignment of interventions: allocation

### Sequence generation {16a}

Following the recruitment of 12 schools, schools will be randomly allocated to each of the study groups. The allocation sequence will be generated using Microsoft Excel by the project statistician not involved in the data collection.

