### Trial design {8}

This study is a three-arm parallel design, superiority, cluster-randomized controlled trial comparing three interventions. Interventions will be applied at the cluster (school) level. Either active or comparator intervention is administered to the school by randomization to prevent contamination. The allocation ratio is 1:1:1.

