## Methods: participants, interventions, and outcomes

### Study setting {9}

This study will be carried out in 12 secondary schools in Hong Kong, the primary sampling unit, and formed the clusters of the trial. A list of secondary schools will be obtained from Hong Kong Education Bureau (https://www.edb.gov.hk/en/student-parents/sch-info/sch-search/schlist-bydistrict/index.html). To balance the social-economic status, 3 local co-educational public or government-subsidized schools from Hong Kong Island, 6 from Kowloon, and 3 from New Territories will be selected and randomly allocated to the 3 groups within each geographical region of Hong Kong.

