## Sample size {14}

The sample size has been calculated using G*Power software. Our previous study showed that motivational interviewing was more effective than prevailing OHE in preventing dental caries among adolescents [17]. In this proposed study, the sample size is calculated based on mean and standard deviations of the primary outcome measure — the number of new carious teeth (∆DMFT). From the pre-existing study, an effect size of 0.21 was obtained for tooth status over 24-month evaluation (∆DMFT: test group=0.12 vs. control group=0.34; SD ~ 0.50) [18], which could be considered a moderate size convention for 1-way ANOVA and clinically significant for the primary outcome [19]. Based on a significance level of 5% and a targeted statistical power of 80%, 74 participants in each group will be required. Considering a typical value of ICC = 0.03 in a cluster randomized clinical trial setting [20] and if 75 children are to be recruited from each school, the design effect will be 3.22 [21]. Assuming a similar dropout rate as our previous study in secondary school at the 2-year follow-up (dropout rate: 10%) [17], the sample size will be increased to 300 in each group, thus 900 altogether. Then 4 schools in each group, a total of 12 schools will be recruited.

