### Concealment mechanism {16b}

The allocation sequence concealment will be ensured as the statistician will not release the allocation sequence until the baseline data collection has been completed.

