## Data collection and management

### Plans for assessment and collection of outcomes {18a}

The data collection will involve oral examination and questionnaire surveys. Students will have oral examinations at school at baseline, 1-year, and 2-year follow-up by one or two trained, experienced, and calibrated examiner(s). An intra-oral LED light, disposable mouth mirrors, and WHO dental probes will be used during the clinical examination. No x-ray will be taken. Inter-examiner and intra-examiner reliability will be assessed.

Self-completed questionnaires will be delivered to the students at baseline, 6 months, 1-year, and 2-year follow-up through the schools. The items in a validated oral health behavior questionnaire for adolescents based on the health belief model (OHBQAHBM) will be used [22].

Information on the social-demographic backgrounds of the family will also be collected.

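### Schools are balanced on region only, although allocation is already withheld until baseline is complete: drawing from a balanced subset would cheaply reduce chance imbalance between arms of 4 schools

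*Protocol article*

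**What the plan says.** - **Number of schools.** Sample size {14}: "Then 4 schools in each group, a total of 12 schools will be recruited". Trial design {8}: "The allocation ratio is 1:1:1".
- **Restriction.** Study setting {9} gives the aim as "To balance the social-economic status". It takes 3 "schools from Hong Kong Island, 6 from Kowloon, and 3 from New Territories will be selected", and these are "randomly allocated to the 3 groups within each geographical region of Hong Kong". Each arm therefore receives one Hong Kong Island, two Kowloon and one New Territories school. No other balancing factor is named.
- **Generation.** Sequence generation {16a}: "Following the recruitment of 12 schools, schools will be randomly allocated to each of the study groups". This section does not repeat the region strata.
- **Release.** Concealment mechanism {16b}: "the statistician will not release the allocation sequence until the baseline data collection has been completed". Implementation {16c} agrees: the research assistant learns the assignments only after baseline.
- **Baseline data.** Plans for assessment and collection of outcomes {18a}: "Students will have oral examinations at school at baseline, 1-year, and 2-year follow-up". Questionnaires are also given at baseline. Family background is collected, but no time point is stated for it.
- **Analysis.** Statistical methods {20a} adjusts for gender and parental education and includes a school-level random intercept. Baseline caries is not a named covariate.

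**The concern.** The trial accepts the delay of holding back the allocation until baseline is done, but uses that delay only for concealment. The baseline examinations would let the statistician see which allocations put, say, the schools with most caries together in one arm, and avoid them. Region is a proxy for socio-economic status. How well it tracks school caries levels or parental education is unknown, and 4 schools per arm leave much to chance. At stake are the precision of the arm contrasts and the credibility of a baseline table that may show visible differences. Once schools are told their arm, this cannot be changed.

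**Working it through.** **1. The plan's own figure.** The protocol states no figure for balance, but its 4 schools per arm reproduce. 74 x (1 + 74 x 0.03) = 74 x 3.22 = 238.3; divided by 0.9 this is 265; 265/75 = 3.53, rounded up to 4 schools, or 300 per arm.

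**2. Possible allocations.** Within strata of 3, 6 and 3 schools: 3! x 6!/(2!2!2!) x 3! = 6 x 90 x 6 = 3,240.

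**3. Imbalance in one school characteristic.** Ignoring region, the SD of a difference between two means of 4 schools is sqrt(1/4 + 1/4) = 0.71 school SD. All 3,240 allocations were enumerated for simulated sets of two independent normal school covariates unrelated to region (an assumption; the protocol gives no school-level SDs). Balance was scored by the sum of squared pairwise arm differences. Results per covariate, in SDs of the 12 schools:

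| Draw from | RMS pairwise difference | Mean largest difference | Largest > 0.5 SD | Largest > 1 SD |
|---|---|---|---|---|
| all 3,240 | 0.70 | 0.87 | 79% | 37% |
| best 30% to 25% (972 to 810) | 0.44 to 0.42 | 0.55 to 0.52 | 56% to 52% | 3% to 1% |
| best 10% (324) | 0.32 | 0.41 | 31% | about 0% |

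If region explains 30% of school variance, the 37% becomes about 28-29%. On a population-SD scale rather than the SD of the 12 schools, the two figures are about 33% and 20%.

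**4. How tight the subset may be.** The strata already keep 6 of the 66 school pairs apart (3 pairs in each three-school region). Among the other 60, the best 10% leaves at least one pair never sharing an arm in about 80% of simulated sets. At the best 25-30% this happens in roughly 10-20%.

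**5. Outcome scale.** With the plan's ICC of 0.03 and SD of 0.50, the school SD is 0.50 x sqrt(0.03) = 0.087. The SD of an arm difference from school effects alone is 0.087 x 0.71 = 0.061 teeth, or 28% of the planned difference 0.34 - 0.12 = 0.22. For ICC 0.01 to 0.10 the share is 16% to 51%.

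**6. Gain in the standard error.** With 75 x 0.9 = 67.5 students analysed per school, the SD of a school mean is 0.50 x sqrt(0.03 + 0.97/67.5) = 0.105, and the unadjusted SE of a contrast is 0.105 x 0.71 = 0.074. Let r be the correlation between the balancing variable and the school mean increment. The SE is then multiplied by sqrt(1 - r² + r²q), where q = (RMS after/RMS before)².

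- Best 10%: q = (0.324/0.704)² = 0.21. For r = 0.3, 0.5, 0.7 the SE falls by 4%, 10%, 22%.
- Best 25-30%: q = (0.42/0.70)² = 0.36 to (0.44/0.70)² = 0.40. The SE falls by 3%, 8%, 16-17%. At r = 0.5 this is 0.074 to about 0.068.

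**The case against.** The strongest reply is that nothing here is wrong. Randomising within region is an accepted restricted design, aimed expressly at socio-economic balance. The model already adjusts for parental education and has a school intercept. That stands, and it is why this is an improvement and not a defect.

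A reader might infer that imbalance of this size biases the trial. The documents do not support that: under randomisation, chance imbalance is part of the sampling error that the standard error describes. A reader might also infer that the change removes imbalance. It does not: after a draw from the best 25-30%, the largest difference still exceeds 0.5 SD in more than half of allocations.

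Nor does the change save model terms, since the balancing variables must enter the model either way. Once they do, adjustment recovers part of the same precision, so the percentages above describe the unadjusted SE only.

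The objection on timing also has weight. The protocol ties release, not generation, to the end of baseline, and does not say expressly that all 12 schools must finish first. Data management {19} describes paper charting, data entry and a second person's proofreading. Trial status ends recruitment in June 2023 and the project in June 2025, which leaves little slack. The baseline data are collected before release, but are not necessarily ready for use.

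What does not stand is that the timing defeats the proposal. Allocation already waits for baseline collection, so the extra wait is for school-level summaries of a few variables.

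**Conclusion.** The point holds as a worthwhile, inexpensive improvement. Region is the only balancing factor named, there are 4 schools per arm, and baseline collection precedes release. For a characteristic unrelated to region, the largest pairwise difference exceeds 1 school SD in about 37% of allocations; if region explains 30% of school variance, in about 20-29% depending on the SD used. A draw from the best 25-30% brings the 37% down to 1-3%. The gain in the unadjusted SE is about 3-17% for correlations of 0.3 to 0.7, and no passage gives that correlation. The results assume independent, normally distributed school covariates, and more than two balancing variables would dilute the benefit.

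The silence of {16a} on strata might be read as a switch to unrestricted allocation. Study setting {9} states the strata plainly, so this is an omission to tidy up, not a contradiction.

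**What to change.** In Sequence generation {16a} and Concealment mechanism {16b}:

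- Restate the region strata of Study setting {9}.
- State that the sequence is generated, not only released, once baseline is complete in all 12 schools.
- Have the statistician list the 3,240 region-stratified allocations, score each on school mean baseline caries and parental education, and draw one at random with a recorded seed from a pre-specified best-balanced subset of about 25-30%.
- Beyond the pairs that the strata themselves separate, check that no two schools are forced together or apart, and widen the subset by a pre-stated rule if any are.

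In {18a}, state that parental education is collected at baseline. In {20a}, include both balancing variables in the primary model.

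**Cost.** Protocol wording, a few hours of the statistician's time, and no new measurements. The real price is that baseline caries and parental education must be entered and summarised for all 12 schools before the draw, which may slightly delay the start of messaging. If regions had to be released separately, the method could be used only within Kowloon (90 allocations).

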### Concealment mechanism {16b}

The allocation sequence concealment will be ensured as the statistician will not release the allocation sequence until the baseline data collection has been completed.

### Implementation {16c}

The project research assistant will enroll the participants via the principal of the school. He/she will be informed of the intervention assignments of the study clusters after baseline data collection and then assign participants to interventions and in charge of implementing different interventions correspondingly.

## Assignment of interventions: blinding

### Who will be blinded {17a}

In the present study, the outcome assessors (dental examiners), and data analysts will be blinded to the group assignment of the study participants. Dataset submitted to the data analysts will only contain group numbers whereas the intervention strategy is blinding. Masking of participants would be impossible because the consent procedure required by the Ethics Committee informing participants about the content of the study.

### Procedure for unblinding if needed {17b}

There is no anticipated harm to trial participants so there is no plan for unblinding.

## Data collection and management

### Plans for assessment and collection of outcomes {18a}

The data collection will involve oral examination and questionnaire surveys. Students will have oral examinations at school at baseline, 1-year, and 2-year follow-up by one or two trained, experienced, and calibrated examiner(s). An intra-oral LED light, disposable mouth mirrors, and WHO dental probes will be used during the clinical examination. No x-ray will be taken. Inter-examiner and intra-examiner reliability will be assessed.

Self-completed questionnaires will be delivered to the students at baseline, 6 months, 1-year, and 2-year follow-up through the schools. The items in a validated oral health behavior questionnaire for adolescents based on the health belief model (OHBQAHBM) will be used [22].

Information on the social-demographic backgrounds of the family will also be collected.

### Plans to promote participant retention and complete follow-up {18b}

Follow-ups will be incentivized by offering participants a set of adolescent oral health care products upon completion of each follow-up assessment.

### Data management {19}

All data collection of the clinical charting form will take place physically in the school and will be recorded in hard copy. The questionnaire will be distributed via school, the research team will collect it on the day of the dental checkup. The research assistant will check out the missing data or unreasonable information, and amend the response via phone call or mobile messages.

Data entry and coding will be completed by a research assistant. To ensure accuracy, data proofreading and range checks for data values will be applied by another research assistant. A regular check will be run for data consistency and quality by project investigators.

All the hard copies of the clinical charting form and questionnaire will store in locked cabinets in the Faculty of Dentistry HKU. The dataset will be kept in a secured computer server equipped with a firewall password. The data only can be accessed by the ethics committee, the Institutional Review Board (IRB) of the University of Hong Kong/Hospital Authority Hong Kong West Cluster, and the research team. The participating schools will not obtain and maintain any individual research data.

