### Confidentiality {27}

The research data will be handled in line with the Hong Kong Hospital Authority’s policy in handling/storage/destruction of patients’ medical records.

During the trial, a de-identified database in which the student and parent names and contact numbers are eliminated will be for exchange among research team members and analyses. Only the research assistant responsible for the mobile messaging could access the password-protected file with participant identifying information. All the personal data will be destroyed after 3-years of storage.

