### Methods in analysis to handle protocol non-adherence and any statistical methods to handle missing data {20c}

The non-adherence of study participants will be recorded (e.g., crossing over to the other randomized group or registering another oral health promotion project). The reasons for withdrawal will also be asked and recorded. Intention-to-treat (ITT) approach will be used for data analysis.

In cases with missing data (particularly for the questionnaire), telephone calls or text messages will collect the missing information. If failed, the data imputation will perform using the mean/mode of the variable from the same group of participants if the missing data is less than 20%. If there is missing data in the follow-up, the last observation carried forward method will be adopted. If 20% or more of the data is missing, then the case will be excluded from the data analysis. The sensitivity analyses will perform to see how great is the impact of missing data and how different data imputations may affect results.

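### Follow-up questionnaire answers can be re-elicited and amended by the unblinded assistant who delivers the messages, an avoidable arm-related source of bias in the self-reported secondary outcomes

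*Protocol article*

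**What the plan says.** Students complete the questionnaires themselves at baseline, 6 months, 1 year and 2 years (Plans for assessment and collection of outcomes {18a}). Data management {19} then provides: "The research assistant will check out the missing data or unreasonable information, and amend the response via phone call or mobile messages". This covers answered items that look implausible as well as blanks. The missing-data section {20c} uses the same route as its first step for questionnaire gaps: "telephone calls or text messages will collect the missing information".

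On who knows the arm, Implementation {16c} says of the project research assistant: "He/she will be informed of the intervention assignments of the study clusters after baseline data collection and then assign participants to interventions". The same sentence makes that person "in charge of implementing different interventions correspondingly". On who can reach participants, Confidentiality {27} describes the team's shared file as "a de-identified database in which the student and parent names and contact numbers are eliminated", and adds: "Only the research assistant responsible for the mobile messaging could access the password-protected file with participant identifying information". On blinding, section {17a} says that "the outcome assessors (dental examiners), and data analysts will be blinded to the group assignment". It lists no other blinded role and states that participants cannot be masked.

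**The concern.** A self-completed answer is useful in an open-label behavioural trial partly because no one connected with the intervention stands between the student and the form. Once an answer is queried by the person who delivers the intervention and knows the arm, it becomes a provider-elicited answer. Knowledge of the arm can affect which answers look implausible, how the question is put again, and what the student feels is the expected reply.

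This pressure need not be equal across arms. In the two messaging arms, stage II asks students how often they brushed twice daily and how often they took sweet drinks, and sends praise in return. A student there who is re-asked by the same sender is answering a coach. A student in the pamphlet arm has had no such exchange. The expected direction favours the messaging arms on outcomes iii to vi, four of the six secondary outcomes. Behaviour change comes first in the stated objective, so these outcomes matter to the trial's message. Blinded analysts cannot undo the effect, because they receive values that have already been amended.

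**Working it through.** The protocol gives no figure to reproduce, so the check sets its sections side by side.

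1. **What is done.** Data management {19} and section {20c}: missing or implausible answers are followed up by phone or message, and the response is amended.

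2. **What that requires.** The caller needs a name and a number. Confidentiality {27} removes both from the shared database and restricts the identifying file to the assistant responsible for the messaging.

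3. **What that person knows.** Implementation {16c}: the project research assistant is told the cluster assignments after baseline and implements the interventions. Whoever sends arm-specific messages must in any case know the arm.

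4. **Whether that role is blinded.** Section {17a} names dental examiners and data analysts only.

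5. **Whether another step protects the data.** Data management {19} gives a second assistant proofreading and range checks. These test whether values are plausible and correctly entered. They would not detect a shift related to arm. The article does not say that this assistant is blinded, and the access rule gives that person no contact details.

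Steps 1 to 4 together mean that, under the plan's own access rule, the person able to amend a follow-up answer is the unblinded intervention provider.

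**Which outcomes.** Section {18a} names oral examination and questionnaires as the outcome data sources. Outcome vi (self-efficacy) is expressly a questionnaire score. Outcomes iii to v (toothbrushing, sugary snack and drink frequency, free-sugar amount) are not tied to an instrument in Outcomes {12}. They are not examination findings, so the questionnaire is the inferred source. Caries, BOP% and VPI come from blinded examiners and lie outside this point.

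**Which waves.** Under the concealment and implementation sections, the allocation is released only after baseline data collection. The three follow-up waves are exposed and baseline is not. Weekly messages run for 24 weeks, so the contrast in coaching should be sharpest around the 6-month questionnaire. Strategies to improve adherence {11c} adds three-monthly contact with the intervention groups and states no end date, so later waves cannot be ruled out.

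**Size.** In a between-arm difference in proportions, the bias is roughly (share of answers amended) × (extra shift in one arm among amended answers). The protocol supplies neither factor.

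**The case against.** The strongest objection is about identity. No sentence says that the person who amends answers is the person who sends messages. The article speaks of the project research assistant, the research assistant, another research assistant, and the one responsible for messaging, which suggests more than one. This stands as a limit: the link is inferred. The inference is firm, because the stated method of amendment needs contact details that the stated access rule gives to one role only. Schools could offer another route to students, but that is not the method described.

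Second, participants are unmasked, so self-report is already open to arm-related bias. True, but the amendment step adds a second source, and this one can be avoided.

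Third, re-asking a respondent is an ordinary data query, and scripts or audit trails usually sit in a fuller document. Their absence from a journal article is not the point here. The point is the combination that the article does state: the method, the access rule and the list of blinded roles.

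Fourth, for blank items there is no earlier answer to shift from, and the plan's fallback is group mean or mode imputation. It is not shown that asking is worse than imputing. That stands, and it is a reason to move the query to someone else and not to abolish it.

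Two stronger readings are tempting and fail. A reader might say that only the messaging arms are reached by phone, but the pamphlets also go out by mobile messaging. The arms differ in coaching, not in medium. A reader might also put a number on the bias: with 5–20% of answers amended and a 10–30 percentage-point differential shift, 0.05 × 10 = 0.5 and 0.20 × 30 = 6 percentage points. Every input there is assumed. The 20% in section {20c} separates imputing from excluding and is not a query rate, so this range is not evidence of size.

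**Conclusion.** The point holds as a weakness in design and data handling. As written, the plan lets the unblinded intervention provider re-elicit and amend self-reported answers at 6 months, 1 year and 2 years, which adds an avoidable, arm-related source of bias to secondary outcomes iii to vi. The conclusion rests on two inferences: that the amender is the holder of the contact file, and that outcomes iii to v come from the questionnaire. The direction, towards the messaging arms, is what one would expect but is not demonstrated. The size cannot be estimated from the document and may be small if few answers are queried. The primary outcome, BOP%, VPI and all baseline answers are unaffected. The plan should be changed because the change is cheap and because an answer overwritten without a record may not be recoverable.

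**What to change.** Amend Data management {19}, Confidentiality {27} and the missing-data section {20c} together:

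1. Check each questionnaire for blanks when it is collected, at every wave. Tie this to collection itself and not to the dental check-up, because section {18a} schedules no examination at 6 months.
2. Give later queries to an existing assistant who sends no messages and is kept unaware of allocation. That assistant works from a contact list without arm labels and from a neutral script. Widen the access rule in {27} to permit this; otherwise the sections would contradict each other. Since whole schools are allocated, the school-to-arm key must also be withheld from this assistant.
3. Always keep the original answer. Log any correction that the respondent confirms beside it, and add a sensitivity analysis on the unamended answers to those already foreseen in {20c}. Genuine recording errors can then still be corrected.

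Cost: wording changes in three sections, a reallocation of tasks between assistants, restricted contact access for one more staff member, and a little extra record-keeping and analysis. A student may still reveal the arm during a call, so the risk is reduced and not removed.
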